In addition, we will study the role of bacterial and viral co-infections. Co-infections can account for up to 30-50% of the cases of M pneumoniae infection. (4, 15, 16) Infection with M. pneumoniae is frequently associated with infections with S. pneumoniae and respiratory viruses. This association might be due to damage to the respiratory epithelium by a virus facilitating infection with M. pneumoniae. However, virtually nothing is known regarding this issue. Children younger than 5 years frequently suffer from viral respiratory infections, which might support the data that M. pneumoniae infections in this age-group are more frequent than previously thought. It is also unknown whether viral co-infection leads to more severe clinical disease. This study aims to answer these questions.

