# STUDY DESIGN

**Aim I: To optimize the diagnosis of M. pneumoniae infections using quantitative PCR**

We will initiate our investigations in a well-defined and easy accessible study population. Children visiting the Emergency Department of the Erasmus Medical Center/Sophia Children’s Hospital in Rotterdam because of suspected respiratory tract infection will be asked to participate in this study. Since this department has an open environment, many children present with symptoms of both upper and lower respiratory tract infections, submitted by a general practitioner as well as by themselves or their parents. In fall 2009 the recruitment of group A will be extended by pediatric patients attending the General Practitioner’s Service, in this protocol referred to as HAP (Huis Artsen Post).

Group B, consisting of healthy controls, will be recruited from children undergoing surgery at the Erasmus MC/ Sophia Children’s Hospital. Many children need to have surgical procedures for reasons that are not in any way related to the exclusion criteria of our study. These children, who have not suffered from an RTI over the previous two weeks and who have not used antibiotics in the preceding 48 hours, are considered eligible for inclusion. The main reason to address these children instead of approaching schools and day care centres is the fact that children undergoing a surgical procedure are drugged by anaesthetics anyway. This way the burden for healthy controls will be minimized.

*Clinical samples*

From each patient the following samples will be obtained

- Oropharyngeal swab
- Nasopharyngeal swab
- Nasopharyngeal lavage
- Serum (blood sample of 200 microliters)

In group A second serum samples will be taken 2-3 weeks after the first visit.

*Clinical data*

For each patient, patient characteristics, time of onset of illness, clinical signs and symptoms, use of antibiotics, laboratory results and radiological findings, treatment, complications, and hospitalization will be documented in a standardized questionnaire. Based on clinical data different diagnosis will be made. This will be divided in lower respiratory tract infections (such a pneumonia and bronchiolitis) and upper respiratory tract infections (such as pharyngitis). Severity of disease will be determined by days of required oxygen or mechanical ventilation.

*Detection of M. pneumoniae*

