All swabs will be washed out in a buffer, which allows bacterial culturing as well as total nucleic acid (DNA and RNA) purification. Material will be frozen at -80C and analyzed as a batch. Purified nucleic acids will be used in real-time PCR assays for the detection of M. pneumoniae.

M. pneumoniae will be detected and quantified using a quantitative, real-time (TaqMan®) PCR assay that has recently been developed in the Laboratory of Pediatrics by Dr. [name].

RTI by M. pneumoniae will be defined by RTI symptoms in combination with serology and/or culture positive for M. pneumoniae and/or conventional PCR for M. pneumoniae.

Aim II: To study the role of host factors (age, and bacterial and viral co-infection) on infection by M. pneumoniae

*Approach*

See aim I

*Clinical samples*

See aim I

*Clinical data*

See aim I. Virulence will be defined by disease severity (determined by hospitalization and duration of hospitalization).

*Detection of M. pneumoniae and other bacteria and viruses:*

See aim I. The other bacteria that will be investigated are S. pneumoniae, Staphylococcus aureus, Haemophilus Influenzae and Moraxella catarrhalis. These bacteria will be detected using routine, conventional bacterial culturing. In collaboration with the department of virology ([name]. [name]), the following respiratory viruses will be detected by real-time PCR: influenzaviruses, parainfluenzaviruses, rhinoviruses, respiratory syncitial virus (RSV), coronaviruses and human metapneumovirus (hMPV).

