Below five years of age there’s a high prevalence of viral infections. It is therefore necessary to use a greater number of children with RTI in that group to find a reasonable number of M. pneumoniae infections. Using a pre-calculated number of children < 5 years (400) and > 5 years (100), the detectable difference will be 12 % assuming prevalence up to 10% in the < 5 years of age group.

Question 5 (objective 2): do children with M. pneumoniae and a viral or bacterial co-infection have more severe illness?

Analysis: children in group A with a RTI caused by M. pneumoniae will be divided in two groups: children without co-infection, and children with a viral or bacterial co-infection. Severity of disease will be scored according to diagnosis, severity of respiratory distress (days of required oxygen or mechanical ventilation and days of hospitalization. Groups will be compared using Mann-Whitney U test.

Question 6 (objective 3): does genotype of M. pneumoniae influence the rate of asymptomatic carrier state (level of PCR in healthy children, group B), and/or severity of disease?

Analysis: depending on the number of different genotypes of M. pneumoniae found, we will compare these different genotypes to PCR levels using Kruskal-Wallis test. This will be done in the asymptomatic children (healthy M. pneumoniae carrierstate) as well as the children with a M. pneumoniae RTI. Severity of disease will be scored according to severity of respiratory distress (days of required oxygen or mechanical ventilation) and days of hospitalization. This will be compared with different genotype by Kruskal-Wallis test in the symptomatic group (children with M. pneumoniae RTI).

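### Question 5 compares severity by co-infection without accounting for age, and the protocol defines severity differently in four places

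*Protocol*

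**What the plan says.** **Comparison.** Section 9, Question 5, takes group A children whose RTI is caused by M. pneumoniae and forms two groups: "children without co-infection, and children with a viral or bacterial co-infection". The test is fixed: "Groups will be compared using Mann-Whitney U test". There is no age stratum or covariate. Section 7.1 lists the relation between co-infection and virulence among the main endpoints, and names no secondary endpoints.

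**Age.** Section 1 states that "Children younger than 5 years frequently suffer from viral respiratory infections". Sections 4.4 and 9 (Question 4) repeat the point to justify recruiting more young children. Section 4.1 fixes group A at 400 children under 5 and 100 aged 5 or over.

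**Severity.** It is defined in four places:

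- Section 3, Aim I: "Severity of disease will be determined by days of required oxygen or mechanical ventilation".
- Section 3, Aim II: "Virulence will be defined by disease severity (determined by hospitalization and duration of hospitalization".
- Section 9, Question 5: "Severity of disease will be scored according to diagnosis, severity of respiratory distress (days of required oxygen or mechanical ventilation and days of hospitalization".
- Section 9, Question 6: "scored according to severity of respiratory distress (days of required oxygen or mechanical ventilation) and days of hospitalization".

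**The concern.** Age is a candidate confounder. The Protocol ties viral infection to young age, so the co-infected group may well be younger than the other group. If younger children are also admitted, or given oxygen, more often or less often for reasons unrelated to co-infection, the crude comparison mixes the two effects. Age is recorded and is itself a host factor under Aim II, yet the stated test makes no use of it.

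The outcome is a separate problem. A Mann-Whitney test needs one ordered value per child. The four definitions have different components, and none says how a diagnosis and two counts of days become a single score. Question 5 serves Aim II, whose own definition contains neither diagnosis nor oxygen days. Unless one rule is set in advance, the score can be chosen after the data are known.

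**Working it through.** The Protocol gives no sample size, effect or power for Question 5, so there is no figure of its own to reproduce. The check asks how far age alone could move the result.

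**Inputs from the Protocol**

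- Group A: 400 under 5 and 100 aged 5 or over (section 4.1).
- M. pneumoniae infection: up to 10% under 5, with a detectable difference of 12 points (sections 4.4 and 9). Cases under 5: 400 × 0.10 = 40.
- Cases aged 5 or over: 100 × 0.22 = 22 if the detectable difference is real, or 100 × 0.10 = 10 if prevalence is equal, which is the hypothesis in the Summary. The total is 62 or 50.
- Co-infection: up to 30-50% of M. pneumoniae cases (section 1), not split by age.

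**Assumed, because the Protocol does not give them:** co-infection share *c* and admission share *h* in each age group.

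**Crude admission with no co-infection effect within age group** (y = under 5, o = 5 or over)

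- Co-infected: (n_y·c_y·h_y + n_o·c_o·h_o) / (n_y·c_y + n_o·c_o)
- Not co-infected: the same with 1 − c in place of c

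Scenario A, 40 + 22 cases, co-infection 60% / 25%, admission 40% / 10%:

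- Co-infected: (9.6 + 0.55) / (24 + 5.5) = 10.15 / 29.5 = 34.4%
- Not co-infected: (6.4 + 1.65) / (16 + 16.5) = 8.05 / 32.5 = 24.8%

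This is a gap of almost 10 points, all of it due to age.

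**Error of the stated test.** Simulation with 4,000 replicates per cell. Hospital days were zero if not admitted and otherwise 1 + Poisson(2). Two-sided 5% Mann-Whitney and van Elteren (strata <5 / ≥5) tests were applied.

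| Scenario: co-infection; admission (<5 / ≥5) | Cases | Overall co-infected | Crude admission, co-infected vs not | Mann-Whitney | Stratified |
|---|---|---|---|---|---|
| A: 60/25; 40/10 | 40 + 22 | 48% | 34% vs 25% | 12% | 5% |
| B: 70/20; 50/10 | 40 + 22 | 52% | 45% vs 26% | 30-31% | 4% |
| C: 50/30; 40/20 | 40 + 22 | 43% | 35% vs 31% | 6% | 5% |
| A | 40 + 10 | 53% | 37% vs 30% | 7% | 5% |
| B | 40 + 10 | 60% | 47% vs 34% | 13% | 5% |
| C | 40 + 10 | 46% | 37% vs 35% | 5% | 5% |

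Two further checks, both with co-infection 70/20:

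- Admission 40% in both age groups: the unadjusted error is 5% for either case count.
- Admission reversed, 25% under 5 and 50% at 5 or over, 40 + 22 cases: co-infected (7 + 2.2) / 32.4 = 28.4%, not co-infected (3 + 8.8) / 29.6 = 39.9%, with rejection in about 14 to 15% of runs. The spurious difference now points the other way.

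The stratified test stayed between 4% and about 6% in every scenario run.

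**Severity definitions side by side**

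| Place | Diagnosis | Oxygen / ventilation days | Hospitalization |
|---|---|---|---|
| Aim I | no | yes | no |
| Aim II | no | no | yes, and duration |
| Question 5 | yes | yes | days |
| Question 6 | no | yes | days |

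No two rows are the same. Aim II also refers back to Aim I for its clinical data before giving its own definition, and Aim III, which Question 6 serves, refers back to Aim II.

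**The case against.** The best defence has four parts.

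**The confounding is not shown.** This stands. The Protocol says that viral infections are common under 5. It does not say that co-infection among M. pneumoniae cases varies with age, nor that severity does. A reader might infer that a positive Question 5 result would simply be an age effect. The Protocol does not support that: the size and direction of any bias cannot be derived from it, and with modest age differences the inflation is slight.

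**The larger error rates use a favourable case count.** This also stands. The 22 older cases come from the detectable difference and are not an expected number, so 40 + 10 must be shown beside them. Scenario B also implies 52% or 60% co-infection overall, above the Protocol's upper figure of 50%. A reader might go further and expect the group without co-infection to be very small. At 30-50% co-infection, however, about 25 to 35 of 50 cases would be without it.

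**The severity definitions overlap.** They do so in part. The Question 5 score contains the oxygen days of Aim I and the hospital days of Aim II, and Aim II words its version as a definition of virulence. That reduces the conflict but does not remove it: Question 5 adds diagnosis, Question 6 omits it, and no place is said to govern. A reader might also infer that scoring by diagnosis builds in a link with viral infection. The Protocol does not say which diagnoses are viral, so that argument has no basis in it.

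**The study is explorative, and such detail belongs in an SAP.** This carries less weight. Section 9 already fixes the groups, the components and the test for a question tied to a main endpoint. The point concerns a stated choice and an inconsistency, not missing detail.

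**Conclusion.** The point holds in a limited form. The stated test for Question 5 leaves the result open to an age effect that the Protocol's own account of viral infection makes credible. If both co-infection and severity differ by age, and co-infection has no true effect, the 5% error becomes about 6 to 31% with 40 + 22 cases and about 5 to 13% with 40 + 10. These ranges rest wholly on assumed rates by age. The upper ends need more co-infection than the Protocol expects, and the error stays near 5% if severity does not vary with age.

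The inconsistency in severity needs no assumption. The four definitions differ, and none yields the single ordered score that the test requires.

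**What to change.** 1. In section 9, analyse Question 5 with an age-stratified rank test (van Elteren, <5 / ≥5 years) or with proportional-odds regression that includes age.
2. Reconcile section 3 (Aims I and II) and section 9 (Questions 5 and 6) to one severity definition and one scoring rule, set before the data are seen and used for both questions.
3. Viral and bacterial detection may be examined separately as a supporting analysis. A van Elteren test cannot carry both as separate factors, so this should not be made part of the main comparison.

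**Cost.** The edits are to wording in sections 3 and 9; age and all severity components are already recorded. Expect a small loss of precision with about 50 to 62 cases. With only two strata, some confounding by age can remain among children under 5; regression with age as a continuous term would address part of it.

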# STUDY POPULATION

## Population (base)

Age: 0-16 years

Group A: 500 children visiting the Emergency Department/HAP because of upper or lower respiratory tract infection, from which: 400 children <5 years and 100 children ≥ 5 years.

Group B: 500 healthy controls; recruited from children attending the outpatient clinic in preparation of their surgery. Again: 400 children <5 years and 100 children ≥ 5 years.

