## Sample size calculation

For estimated group sizes in 2 years of 500 in group A and 500 in group B small differences in mean quantitative result of PCR will be demonstrable (α = 0.05, power ≥ 90%) if the effect-size (difference of mean/standard deviation) is 0.20 or larger, which can be considered as a small difference. Group A we aim to include pre-calculated numbers according to age (400 children, < 5 years, versus 100 children, > 5 years). Because of a high prevalence viral RTI below 5 years of age, it is necessary to include more children with RTI in this group, to find a reasonable number of M. pneumoniae infections. Assuming up to 10% M. pneumoniae infections below 5 years of age we will be able to detect a 12% difference using these numbers in these subgroups (< 5 years versus >5 years). For comparison we aim to include the same numbers in group B (healthy children).

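### Question 5 compares severity by co-infection status without age, although the protocol ties viral infection and antibiotic choice to age, so the contrast can mix an age effect with a co-infection effect

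*Protocol*

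**What the plan says.** In Section 9, Question 5 asks whether co-infection goes with more severe illness among group A children whose RTI is caused by M. pneumoniae. The two groups are "children without co-infection, and children with a viral or bacterial co-infection". On the outcome, the plan says: "Severity of disease will be scored according to diagnosis, severity of respiratory distress" (days of oxygen or ventilation), with days in hospital added. On the test: "Groups will be compared using Mann-Whitney U test". No stratification, matching or regression on age appears there or elsewhere in the protocol. The age split is used as an analysis factor only in Question 4.

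On age and viral infection:
- Section 1: "Children younger than 5 years frequently suffer from viral respiratory infections".
- Section 4.4: "Because of a high prevalence viral RTI below 5 years of age, it is necessary to include more children with RTI in this group".
- Section 9, in the paragraph just before Question 5: below five years there is "a high prevalence of viral infections".

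On age and treatment, Section 1 says that first-choice antibiotics differ below and above 5 years, that β-lactams do not work against M. pneumoniae, and that macrolides can markedly shorten the illness.

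Group A is recruited by age quota: "400 children <5 years and 100 children ≥ 5 years" (Section 4.1).

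**The concern.** Age confounds the comparison if it is related both to co-infection and to severity. The protocol supports the first link for viral co-infection. For the second it gives a route but no figure. Treatment follows age, treatment can alter illness duration, and the score counts days of oxygen, ventilation and hospital stay. The score also includes diagnosis, and bronchiolitis is one of the diagnoses listed under Aim I.

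Section 1 asks whether viral co-infection leads to more severe disease, and Section 7.1 lists the relation of co-infections to virulence among the main endpoints. An unadjusted difference cannot say which of the two host factors named in objective 2 produced it. The age mix that it averages over is partly an artefact of the 400/100 quota. The bias could also run the other way, for example if older children present only when severely ill. More cases would not remove it.

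**Working it through.** Question 5 has no sample size, power or effect size, so there is no figure of its own to reproduce.

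**Case numbers.** Two scenarios follow from the protocol.
- Equal prevalence. The Summary hypothesises that infection is as frequent under 5 as above, and Section 12.1.4 expects 10% positive RTI. This gives 0.10 × 400 = 40 and 0.10 × 100 = 10 cases, 50 in all.
- Prevalence differing by the stated detectable 12 points, 10% v 22%. This gives 40 and 22 cases, 62 in all. For 400 v 100 the 12 points are about right: at 80% power I get 10.9 points, or 11.6 with continuity correction.

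**Assumed, not in the documents.** Co-infection shares by age (under 5 / 5 and over) are 50/30%, 50/20% or 60/20%. Section 1 gives only an overall figure: "Co-infections can account for up to 30-50% of the cases of M pneumoniae infection". At 60/20% the overall share is (24 + 4.4)/62 = 46% with 40 and 22 cases, and (24 + 2)/50 = 52% with 40 and 10, just above that range. Admission is 40/20%, 40/10% or 50/10%. Co-infection has no effect within an age stratum.

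**Age mix of the comparison group** (children without co-infection), share aged 5 or over:
- 40 and 22 cases, 60/20%: 0.8×22 / (0.4×40 + 0.8×22) = 17.6/33.6 = 52%.
- 40 and 22 cases, 50/30%: 15.4/35.4 = 44%.
- 40 and 10 cases, 60/20%: 8/24 = 33%.
- 40 and 10 cases, 50/30%: 7/27 = 26%.

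**Spurious admission difference**, co-infected minus not, at co-infection 60/20% and admission 40/10%:
- 40 and 22 cases: (24×0.4 + 4.4×0.1)/28.4 − (16×0.4 + 17.6×0.1)/33.6 = 35.4% − 24.3% = 11 points.
- 40 and 10 cases: (24×0.4 + 2×0.1)/26 − (16×0.4 + 8×0.1)/24 = 37.7% − 30.0% = 8 points.

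**Rejection rates at two-sided 0.05.** Severity is 0 if not admitted, otherwise 1 + Poisson(2.5) days; 6000 simulated studies per scenario. The stratified test sums, over the two age strata, (rank sum of co-infected − n₁(N+1)/2)/(N+1) and divides by its standard error (van Elteren).

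| Cases <5 / ≥5 | Co-infection | Admission | Mann-Whitney | Stratified |
|---|---|---|---|---|
| 40 / 10 | 50/30% | 40/20% | 5% | 5% |
| 40 / 10 | 60/20% | 40/20% | 6% | 5% |
| 40 / 10 | 60/20% | 40/10% | 8% | 5% |
| 40 / 10 | 60/20% | 50/10% | 9% | 5% |
| 40 / 22 | 50/30% | 40/20% | 6% | 5% |
| 40 / 22 | 60/20% | 40/10% | 15% | 4–5% |
| 40 / 22 | 60/20% | 50/10% | 22% | 5% |

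**Sensitivity to the outcome model.** With a normal severity score, 3000 runs per scenario, and under-5s more severe by 0.5, 0.8 or 1.0 SD:
- 40 and 22 cases: 10%, 19% and 26% at 60/20%; 6.5%, 9% and 9% at 50/30%.
- 40 and 10 cases: 7%, 10% and 13% at 60/20%; 5–7% at 50/30%.
- Age effect reversed (−0.5 SD), 60/20%, 40 and 22 cases: spurious difference −0.18 SD, rejection 11%.
- Equal co-infection shares by age, or no age effect on severity: about 5%.

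The stratified test stays at about 4–6% throughout.

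**The case against.** The strongest reply is that the second half of the confounding argument is not in the protocol. No age effect on severity among M. pneumoniae cases is stated, and every gradient above is an assumption. The statements about viral infection in Sections 4.4 and 9 concern all children with RTI, as a reason for recruiting more under-5s. They give no co-infection share among M. pneumoniae cases. The exposure also includes bacterial co-infection, for which no age pattern is stated, and this may dilute the imbalance. The simulated outcomes only stand in for a score that also includes diagnosis and oxygen or ventilation days. All of this stands, and it limits what can be said about size and direction.

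The study calls itself explorative, Question 5 is one of six questions, and adjustment is often left to a statistical analysis plan. The first two points lower the stakes. The third carries less weight, because the protocol does not leave the test open: it names an unadjusted one.

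A reader might infer that viral infection is concentrated under 5, so that the comparison children are mostly older. The protocol says only that viral infection is highly prevalent in that group. Given the quota, 26% to 52% of the comparison children are 5 or over in these scenarios. Confounding needs an imbalance, not a majority.

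**Conclusion.** The point holds in a limited form. Question 5 fixes a test that ignores age, the protocol itself gives reasons to expect co-infected children to be younger on average, and it describes a treatment route by which age could affect the outcome. The contrast can therefore mix an age effect with a co-infection effect.

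Under the protocol's own expectation of similar prevalence by age, the false-positive rate in the admission model is about 5–8%, or 9% under the strongest admission gap. If prevalence differs by 12 points it is about 6–22%. The normal-score model reaches 13% and 26% respectively at its largest age effect. All these figures rest on assumed gradients.

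A reader might take 15% or 22% as the expected error rate, or conclude that a positive result would be due to age. The documents support neither. The 22% prevalence behind those rates comes from a detectable difference, not an expected value, and the bias could be negligible or reversed. This is an inexpensive improvement to an exploratory comparison, not a defect that invalidates the study.

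**What to change.** In Section 9, Question 5, replace the Mann-Whitney test by a Wilcoxon test stratified by the recruitment age strata (<5 and ≥5 years, van Elteren weights), or by a proportional-odds model of severity on co-infection and age. Name one of them as the Question 5 result and report the unadjusted Mann-Whitney result beside it. The stratified test keeps the rank approach; the model can also take up age differences within a stratum.

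The change affects only the wording of Section 9 and needs no new data, since age is already recorded. It loses a little power if age turns out to be unrelated to severity. With about 50–62 cases, precision will be limited under either test. With 10 older cases of whom 20% are co-infected, the older stratum would compare about 2 children with 8.
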